## Abstract

**Background::**

Stroke is the primary cause of adult disability in China, which causes serious personal, family, and social burden. “Central peripheral central” closed-loop rehabilitation theory is proved to be an effective neural rehabilitation model. Based on this theory, repetitive transcranial magnetic stimulation (rTMS) combined with magnetic stimulation of Neiguan (PC6) and Sanyinjiao (SP6) may be an effective treatment for limb dysfunction after stroke. However, the efficacy and mechanism of repetitive magnetic stimulation of M1 region combined with magnetic stimulation of Neiguan and Sanyinjiao points on limb dysfunction after stroke has not been confirmed.

**Methods/Design::**

This study is a prospective, randomized, controlled, open trial. We randomly divided 42 subjects, aged 35 to 80 years, diagnosed with ischemic stroke within 1 month, into 2 groups with a ratio of 1:1. On the basis of this medical treatment, patients in the experimental group received 1 Hz rTMS in M1 area on the contralateral side, and 3 Hz rTMS treatment at Neiguan point and Sanyinjiao point on the affected side. The control group was treated with acupuncture (body acupuncture). All patients were treated once a day and followed up for 10 days. The National Institute of Health Stroke Scale score, simplified fulg Meyer, modified Barthel index, and cortical excitability were evaluated on the day of enrollment and the 10th day of treatment respectively. The modified Barthe index was followed up on the 30th day of treatment, and the adverse reactions were recorded at any time. The mechanism of rTMS will be revealed by Barthe index before treatment, on the 10th day of treatment and on the 30th day of follow-up. The results were analyzed by spss19.0 software, and the quantitative indexes were analyzed by *t* test and rank sum test. *χ*^2^ test was used for non-grade counting, and rank sum test was used for grade counting. All statistical tests were performed with bilateral test. If *P* value is less than or equal to .05, the difference will be considered statistically significant.

**Conclusion::**

The purpose of this study was to determine the effect of repetitive magnetic stimulation of M1 region combined with magnetic stimulation of Neiguan and Sanyinjiao points on limb function after stroke. Through this study, we expect to explore a new scheme for the treatment of poststroke dyskinesia, and prove that compared with rTMS and acupuncture alone, the closed-loop rehabilitation theory based on “center peripheral center” can be more efficient and safe in the treatment of poststroke limb dysfunction.

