However, it is a pity that the mechanism of acupoint magnetic therapy in the treatment of poststroke limb dysfunction is still unclear, and the clinical research is relatively insufficient. To clarify the effect of repetitive transcranial magnetic stimulation M1 combined with repetitive magnetic stimulation at PC6 and SP6 on limb function after cerebral infarction, a prospective randomized, controlled, and open trial was conducted. Forty-two patients with ischemic stroke within 1 month after onset were randomly divided into acupuncture group (control group) and repetitive magnetic stimulation group (experimental group). The purpose of this study is to explore a new method to promote the recovery of limb function after stroke.

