### Study design

2.1

This study is a single-center, randomized, controlled, open clinical trial. A total of 42 participants will be randomly divided into 2 groups with a ratio of 1:1. Both groups were given basic treatment (cerebrovascular disease medical treatment, rehabilitation treatment). In addition to the basic treatment, the experimental group received 1 Hz rTMS in M1 area of the healthy side, and 3 Hz rMS treatment at PC6 and SP6 on the affected side. The control group was treated with acupuncture.

The whole study period was 30 days, including 10 days of treatment and 20 days of follow-up. Before treatment and on the 10th day of treatment and the 20th day of follow-up, the clinical efficacy evaluation scale was used to evaluate the subjects, and the cortical excitability was detected by rMS before and on the 10th day of treatment (Fig. 1).

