#### Positive-control group

2.7.2

In addition to the basic treatment, the patients in the control group also need to be given corresponding acupuncture treatment. According to the theory of traditional Chinese medicine, acupuncture position and parameters were selected^[19,20]^: upper limbs (bilateral): Hegu, Neiguan, Shousanli, Quchi, Jianli; lower limbs (bilateral): Taichong, Xuanzhong, Sanyinjiao, Zusanli, Yanglingquan, Fengshi; head: Baihui, Fengchi (bilateral). Patients will be treated once a day for 10 consecutive days.

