## Discussion

3

Limb dysfunction after stroke is the main complication of stroke and the main cause of adult disability, which seriously affects the working ability and quality of life of stroke patients, and brings serious economic burden to patients and society. With the progress of medical technology, patients have higher expectations of limb function recovery after stroke. Therefore, we designed the clinical research program, hoping to obtain high-quality research data through the improvement of patients’ symptoms and the scale, so as to provide reliable basis for future multicenter research. As a traditional Chinese rehabilitation therapy, acupuncture and moxibustion is widely recognized in the clinical treatment and rehabilitation of stroke. Therefore, we chose the acupuncture program with high public reliability as the control group. PC6 and SP6, as the experimental group, can activate the brain area, increase the link between the brain regions, and strengthen the information exchange between the brain regions. Compared with acupuncture and moxibustion, magnetic stimulation has the advantages of noninvasive, painless, and statistical. In previous clinical trials, it has been confirmed that low-frequency rTMS is of positive significance for the recovery of motor function of stroke patients.^[25]^ However, the use of acupoint magnetic stimulation in the treatment of limb motor dysfunction after stroke is often seen in case reports, and there is no systematic theoretical guidance. The closed-loop rehabilitation theory of “center peripheral center” has great enlightenment on how to improve the treatment effect of limb dysfunction after stroke, but there are few clinical curative effect observation with high confidence based on the “center peripheral center” closed-loop rehabilitation theory. Therefore, based on this theory, we plan to give magnetic stimulation combined with peripheral magnetic stimulation at PC6 and SP6 in central M1 area to observe the effect and difference of acupuncture group on limb function after stroke.

Our scheme is only a pilot study, and its shortcomings include: small sample size, no blindness, short observation time, etc. In the experiment, we will try our best to reduce the error which may affect the research results. Finally, we will prove that rTMS combined with magnetic stimulation of PC6 andSP6 is an effective treatment for limb dysfunction after stroke.

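### The abstract promises superiority over rTMS alone and credits the closed-loop theory, but the two arms can only compare the combined package with acupuncture

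*Protocol article*

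**What the plan says.** **The claim.** The Conclusion of the Abstract first gives a neutral purpose: to determine what M1 stimulation combined with stimulation of the two acupoints does for limb function. It then adds an expectation to explore a new scheme "and prove that compared with rTMS and acupuncture alone, the closed-loop rehabilitation theory based on" a centre-periphery-centre model is more efficient and safe. That names two comparators and credits a theory. The Discussion closes with "Finally, we will prove that rTMS combined with magnetic stimulation of PC6 andSP6 is an effective treatment" for limb dysfunction after stroke.

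**The design.** Section 2.1 states "A total of 42 participants will be randomly divided into 2 groups with a ratio of 1:1". In the first group, "the experimental group received 1 Hz rTMS in M1 area of the healthy side, and 3 Hz rMS treatment at PC6 and SP6"; these points are stimulated only on the paralysed side. For the second, "The control group was treated with acupuncture". Both groups receive the same basic treatment. The Abstract's Methods, the Introduction and sections 2.5, 2.7 and 2.12 agree on two groups, and 2.5 puts 21 patients in each.

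**The theory.** The Introduction presents the closed loop as superposition: a peripheral intervention adds its effect to that of a central intervention that has already activated the brain. The Introduction also calls rTMS an effective central stimulation with evidence behind it, and the Discussion repeats that low-frequency rTMS has helped motor recovery.

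**The concern.** The Conclusion needs two contrasts: the package against acupuncture, and the package against rTMS alone. The design supplies only the first. Crediting the closed loop needs more still, namely evidence that the combination does better than its parts given separately.

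At stake is what may be concluded from a positive result. Readers are likely to carry forward the Abstract's Conclusion, and the Discussion hopes the data will be a basis for later multicentre research. If the package beats acupuncture, the sentence as written would let readers believe that adding acupoint stimulation to M1 rTMS has been shown to help. The trial would hold no information on that.

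**Working it through.** **1. How many arms were sized.** Section 2.11 uses NIHSS means of 8.95 and 6.90, SD 1.93, α = 0.05, β = 0.1 and a multiplier of 10.5.

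- Difference: 8.95 − 6.90 = 2.05.
- Per group: 2 × 1.93² × 10.5 / 2.05² = 18.6, rounded up to 19.
- Total: 19 × 2 × 1.10 = 41.8, rounded to 42.

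The plan's figure reproduces. It is a two-group calculation for one contrast, with no patients allotted to a third group.

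**2. What the two arms identify.** Let B be the mean outcome on basic treatment, C the effect of M1 rTMS, P the effect of PC6/SP6 magnetic stimulation, I any extra effect of giving both, and A the effect of acupuncture.

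- Experimental mean: B + C + P + I
- Control mean: B + A
- The single estimable contrast: C + P + I − A

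The contrasts that the Conclusion needs are:

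| Statement | Contrast | Patients in the comparator | Estimable? |
|---|---|---|---|
| Package better than acupuncture | C + P + I − A | 21 | Yes |
| Package better than rTMS alone | P + I | 0 | No |
| Combination better than each part (superposition) | P + I and C + I | 0 and 0 | No |

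The observed difference fixes C + P + I − A and nothing finer. If P + I = 0, so that acupoint stimulation adds nothing, the difference is C − A. That is positive whenever M1 rTMS outperforms acupuncture. The same positive result is therefore compatible with a closed loop that works and with one that does nothing. More patients would narrow the interval around C + P + I − A but would not separate its terms.

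**3. How the arms differ.** Sections 2.1, 2.7.1 and 2.7.2 side by side:

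| Feature | Experimental | Control |
|---|---|---|
| Central stimulation | M1, healthy side | None |
| Peripheral modality | Magnetic | Needle |
| Side of limb points | Affected side | Bilateral |
| Named points | 2 | 5 upper limb + 6 lower limb + 2 head = 13 |

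The upper-limb list, "upper limbs (bilateral): Hegu, Neiguan, Shousanli, Quchi, Jianli", includes Neiguan (PC6), and the lower-limb list includes Sanyinjiao (SP6). Both acupoints are thus stimulated in both arms, by different means. Four features change at once, so the difference between arms belongs to the package as a whole.

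**The case against.** **It is one phrase, and the rest of the article is narrower.** This stands. The rTMS-alone comparator appears only in the Abstract's Conclusion. The Introduction names acupuncture as the control and speaks of exploring a method, and the Discussion's design paragraph compares with the acupuncture group. No outcome, analysis or sample-size step uses an rTMS-alone contrast. This limits the severity. It does not make the phrase correct, and it shows that suitable wording already exists in the article.

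**Package versus active control is a legitimate design.** This also stands. The Discussion gives its reason for choosing acupuncture. Several components differing at once is inherent to such a comparison and becomes a fault only through the attribution in the Conclusion. A reader might infer that an rTMS-alone, acupoint-alone or basic-treatment-only arm is required. It is not, once the claim is narrowed.

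**The article calls itself preliminary and a pilot.** True, and it lists small size, lack of blinding and short observation as shortcomings. It does not list the missing component comparator, and pilot status sits badly with a promise to prove.

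**The article is condensed.** The arms are described repeatedly and consistently, so a further arm in an unseen document is not plausible.

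**Stronger readings that do not hold.** A reader might infer that the whole Conclusion is untestable; the acupuncture half is tested directly. A reader might expect a non-significant result to be taken as equality with acupuncture; nothing plans that, and section 2.13.1 speaks only of significance showing differences. A reader might want a separate safety finding; section 2.13.3 plans counts, percentages and a χ² test between the arms, and the small sample is already acknowledged.

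**Conclusion.** The Abstract's Conclusion is wrong as written in two respects. It claims a comparison with rTMS alone, for which 0 of 42 patients provide data, and it credits the closed-loop theory when the central and peripheral components are never given apart. Neither can be estimated in this design at any sample size. The comparison with acupuncture, 21 versus 21, is unaffected.

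The closing sentence of the Discussion has a lesser fault. It contains no rTMS-alone comparator, but it announces proof in advance and omits that the evidence will be relative to acupuncture.

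This rests on the two arms being as described throughout the article, and on the ordinary reading of the phrase as rTMS alone and acupuncture alone. It is a correction to the stated conclusion, worth making because it changes what the trial may claim. It does not invalidate the trial.

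**What to change.** **Abstract, Conclusion.** Delete the comparison with rTMS alone and the attribution to the closed-loop theory. Suggested wording: *The trial will estimate the effect of M1 rTMS plus magnetic stimulation at PC6 and SP6, compared with body acupuncture, each added to basic treatment. The separate contributions of the central and peripheral components cannot be distinguished in this design.* The theory can stay in the Introduction as the rationale for the package.

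**Discussion, last sentence.** Replace the promise of proof with the same package-versus-acupuncture aim.

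**Cost.** Wording only: no added arm, patients, visits or analyses. The price is a narrower claim.

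Keeping the rTMS-alone claim would need a third arm. The article gives no rTMS-alone figure, so its size is an assumption. If the 2.05-point difference and SD of 1.93 also held for that contrast, 3 × 19 = 57 patients would be needed, or 57 × 1.10 = 62.7, so 63 with the article's loss allowance. If acupoint stimulation added only half of that difference, the same formula gives 2 × 1.93² × 10.5 / 1.025² = 74.5, so 75 per arm. Narrowing the claim is the proportionate course.

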**Trial Registration::**

The trial was registered in China clinical trial registry (http://www.chictr.org.cn/index.aspx), ID: ChiCTR1900026890 (October 25, 2019)

## Introduction

1

Stroke is one of the main diseases that lead to human death and disability. According to statistics, about 1/7 of women and 1/10 of men in Europe die directly or indirectly from stroke every year.^[1]^ In the United States, 800,000 people suffer from stroke every year. ^[2]^ Stroke is the main disease leading to human disability. About 2/3 of stroke patients have limb dysfunction,^[3]^ which seriously affects people's quality of life and physical and mental health, and brings huge economic and psychological burden to families and society.

Nerve rehabilitation is the main measure to restore limb dysfunction in stroke patients. The traditional rehabilitation treatment mainly includes peripheral intervention measures, such as traditional occupational therapy, physical therapy, acupuncture treatment, etc., all of which are through the continuous input of stimulation from the sensorimotor system to the central nervous system, strengthening the training of the correct movement mode to correct the abnormal movement mode, so as to promote nerve recovery. In particular, acupuncture therapy has been widely used in the rehabilitation treatment of stroke in recent years.^[4]^ However, due to the differences in acupuncture schools, acupuncture methods and acupoint selection, and the stimulation intensity cannot be quantified, the heterogeneity of experimental results is relatively large,^[5]^ and it is difficult to obtain reliable clinical research data.

With the development of rehabilitation technology, through a variety of precise positioning, noninvasive direct brain stimulation in the injured or functional brain areas is gradually emerging. rMS,rTMS,brain-computer interface, mirror therapy, etc. Compared with traditional acupuncture therapy, transcranial magnetic stimulation and peripheral acupoint magnetic therapy can not only play the same therapeutic effect as traditional acupuncture therapy, but also have the advantages of no radiation, no trauma, and quantitative observation of stimulation intensity.^[6]^

To combine the advantages of peripheral and central interventions, a new neural rehabilitation model called “central peripheral central” closed-loop rehabilitation theory was proposed. According to the theory, “peripheral intervention” can superimpose the therapeutic effects of the 2 when the “central intervention” makes the brain area activated, and become a rehabilitation treatment mode with expectant outcomes.^[7]^ Based on this theoretical model, we have worked out a treatment plan of repetitive transcranial magnetic stimulation (rTMS) at Neiguan (PC6) and Sanyinjiao (SP6) for limb dysfunction after stroke.

rTMS is an effective central stimulation for poststroke dyskinesia confirmed by evidence-based medicine.^[8]^ As a noninvasive stimulation technique, rTMS can detect the changes of motor-evoked potential (MEP), electroencephalogram, cerebral blood flow, metabolism, and brain function from the changes of neural activity, especially low-frequency (1 Hz) rTMS can effectively stimulate the central nervous system noninvasively. As a motor center, M1 area of cerebral cortex plays an important role in our limb movement, and has been an effective stimulation target for the treatment of limb dysfunction after stroke.

PC6 and SP6 are the main points of “Xingnao Kaiqiao” acupuncture method in the treatment of stroke, and they are also high-frequency acupoints in the relevant literature on the treatment of stroke.^[9]^ It is found that acupuncture at PC6 in patients with acute cerebral infarction can activate frontal lobe, parietal lobe, and motor area.^[10,11]^ Acupuncture at SP6 in healthy people can activate specific bilateral brain areas such as frontal, parietal, temporal cortex, cingulate gyrus, and thalamus.^[12]^ However, magnetic stimulation of PC6 and SP6 can not only activate brain regions, but also increase the link between brain regions, and strengthen the information exchange between brain regions.^[13]^ This shows that the effect of acupoint magnetic stimulation is similar to that of acupuncture, and compared with acupuncture, magnetic stimulation is noninvasive and pain free, and can improve the compliance of patients.

However, it is a pity that the mechanism of acupoint magnetic therapy in the treatment of poststroke limb dysfunction is still unclear, and the clinical research is relatively insufficient. To clarify the effect of repetitive transcranial magnetic stimulation M1 combined with repetitive magnetic stimulation at PC6 and SP6 on limb function after cerebral infarction, a prospective randomized, controlled, and open trial was conducted. Forty-two patients with ischemic stroke within 1 month after onset were randomly divided into acupuncture group (control group) and repetitive magnetic stimulation group (experimental group). The purpose of this study is to explore a new method to promote the recovery of limb function after stroke.

## Methods/design

2

### Study design

2.1

This study is a single-center, randomized, controlled, open clinical trial. A total of 42 participants will be randomly divided into 2 groups with a ratio of 1:1. Both groups were given basic treatment (cerebrovascular disease medical treatment, rehabilitation treatment). In addition to the basic treatment, the experimental group received 1 Hz rTMS in M1 area of the healthy side, and 3 Hz rMS treatment at PC6 and SP6 on the affected side. The control group was treated with acupuncture.

The whole study period was 30 days, including 10 days of treatment and 20 days of follow-up. Before treatment and on the 10th day of treatment and the 20th day of follow-up, the clinical efficacy evaluation scale was used to evaluate the subjects, and the cortical excitability was detected by rMS before and on the 10th day of treatment (Fig. 1).

**Figure 1 F1:**
[figure not shown]
Flow of subjects randomized to receive acupuncture treatment or rTMS at M1 +rMS at SP6 and PC6 acupiont.

The clinical trial results will be reported according to the Standards for Reporting

Interventions in Clinical Trials of Acupuncture (STRICTA) statement.^[14]^

### Ethics

2.2

This study has passed the ethics committee Shaanxi Provincial Hospital of traditional Chinese medicine ((2019)(32)), and registered on October 5, 2019 at http://www.chictr.org.cn/index.aspx, ID is chictr19000026890. Informed consent has included all the subjects involved. Any modification of the study protocol or informed consent, which may affect the rights and interests of the participants or the implementation of the study, should be reported to the Ethics Committee for approval again. If there are any serious adverse events in the trial, the ethics committee should review it in time and put forward written suggestions for modification, including sufficient power to suspend the trial.

### Study population

2.3

#### Inclusion criteria

2.3.1

1.One month after onset, the patients were diagnosed as ischemic stroke according to computed tomography/magnetic resonance imaging (CT/MRI) examination.2.Aged 35 to 75 years.3.Infarction focus was basal ganglia or (and) radiation coronal area, with unilateral limb paralysis (4 <= National Institute of Health Stroke Scale (NIHSS) <= 15).4.Be conscious and voluntary to join the experiment and sign the informed consent.

#### Exclusion criteria

2.3.2

1.Past history of stroke with limb paralysis.2.Ischemic stroke caused by cardiogenic, other, and unknown causes.3.Patients with severe chronic diseases such as heart, liver, kidney, and hematopoietic system affected the treatment.4.Past history of mental retardation, mental disorder, and epilepsy.5.Indications for thrombolysis.6.Systolic blood pressure (> = 180 mm Hg) or diastolic blood pressure (> = 120 mm Hg).7.The space-occupying effect is obvious, with CT or MRI signs of midline structural displacement.8.Metal foreign bodies exist within 30 cm of the treatment site, such as cochlear implant, built-in pulse generator, aneurysm clamp, stent, metal internal fixation, etc.9.History of alcohol abuse or long-term use of cortical stimulants (sedatives and antidepressants) before illness.

